## **8 STUDY VISITS / PROCEDURES**

### **6.1 Screening**

Potential participants will be identified by local investigators or suitably qualified members of the patient's clinical care team. This may be at routine clinics, during consultations for discussion of treatment or at multi-disciplinary team meetings (MDT's). The Patient Screening Log should be completed for all patients considered for the trial, indicating whether the patient was recruited to the study and if not the reason for this i.e. whether patient declined or was deemed ineligible.

Eligible patients will then be approached about the study at their routine clinic appointment and provided with a Patient Information Sheet (PIS). The local investigator or delegated individual will explain the nature, purpose, and possible benefits and risks of the trial to the patient. If the patient decides to take part in the study they will be asked to complete and sign an Informed Consent Form (ICF).

### **6.2 Informed consent**

Informed consent must be obtained before any study-related activities take place. It is the responsibility of the Investigator or delegate to obtain written consent for each patient prior to performing any trial related procedures. The Investigator may delegate responsibility for obtaining written informed consent to members of the site research team who are appropriately trained in Good Clinical Practice (GCP). Delegation of responsibility must be indicated appropriately on the Site Signature and Delegation Log.

After a patient is approached and provided with a PIS, the patient must be given sufficient time to consider the verbal and written information before deciding to participate. The investigator or delegated individual should discuss the trial clearly and without bias and emphasize that the patient can refuse to participate or withdraw from the trial at any time without giving a reason, and that this would in no way influence their standard of care or relationship with the clinical team. The patient must be given the opportunity to ask questions which should be answered to their satisfaction.

If the patient decides to participate in the study they will be asked to sign and date the current approved version of the ICF. The person taking consent must then also sign and date the ICF. Only patients who are able and willing to give informed consent will be able to participate in the study.

A copy of the ICF should be given to the patient and a copy placed in the patient's notes along with the PIS. The original copy should be stored in the Investigator's Site File (ISF) at each site and a copy must also be sent to Sponsor.

Throughout the study, at each appointment, the patient should be given the opportunity to ask questions about the trial and ongoing consent should be confirmed verbally and recorded in the patient notes. The patient is free to withdraw from the study at any time and any new information relevant to their treatment should be shared with them in a timely manner.

### **6.3 Randomisation**

After signing and dating the Informed Consent Form (ICF) the patient can be entered into the study and randomized. Randomization occurs via a database system at Regional Cancer Center (RCC) within Karolinska Institute, Sweden. In this system the inclusion and exclusion criteria will be automatically verified before patients are randomized. An outline of instructions for randomization can be found in Appendix 2. Full details of how to randomize a patient and access the randomization system will be provided by Karolinska Institute to local sites upon study commencement.

Upon randomization each patient will be allocated a unique Study Identification (ID) number which will be used to identify patients throughout the trial. This Study ID should be recorded on all study documents including the ICF and all CRF's and Questionnaires.

Patients will be randomized to either Group A (without Strattice™) or Group B (with Strattice™). Patients should be informed of their allocation promptly and a letter sent to their GP to inform them of their participation and treatment allocation.

## 6.4 Study settings and procedures

Surgeons performing IBR within the trial will be either plastic surgeons, or breast surgeons familiar with the ADM technique. Training instructions will be provided to reduce variations between centres. The surgical technique using ADM is outlined in Appendix 3.

The decision and treatment plan advocating mastectomy will be based on a multi-disciplinary conference (MDT), and the diagnosis of invasive or pre-invasive (in situ) breast cancer is made on triple assessment. If the patient wishes to undergo immediate implant based reconstruction, and meets the selection criteria for entering the study, they will be approached about the study.

Patients randomized to Group A (non-Strattice™) will be reconstructed with expander or anatomical gel implants without ADM, using complete muscle coverage. Group B (Strattice™) will be reconstructed with expander or anatomical gel implant using partial muscle coverage in conjunction with ADM. Randomization at enrollment is made with regard to the use of ADM or not, so both expander and direct-to-implant techniques will be utilized in both groups, depending on the quality of skin flaps at time of surgery.

All patients randomised to Group A, the standard (non-Strattice™) treatment will undergo a two stage post-mastectomy reconstruction using an expander prior to the implant being fitted. Patients randomised to Group B, the treatment arm using Acellular Dermal Matrix (Strattice™) will either undergo the same two-stage reconstruction but with the addition of the Strattice™ mesh, or a single-stage post-mastectomy direct-to-implant reconstruction which does not use an expander and in which the Strattice™ is fitted in the same procedure as the implant. The type of procedure used will be dependent on clinical factors such as the size and shape of the breasts and the surgeon will make this decision on a case-by-case basis. In cases where an expander is used the tissue expanders will be permanent expanders such as Becker 35 (Mentor©) or Style 150 (Allergan©), or anatomical gel implants such as Mentors© CPG series or from Arion Laboratories©.

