## 4 STUDY SETTINGS

Currently in Oxford, most patients receiving Immediate Breast Reconstruction (IBR) using implants will undergo a two stage post-mastectomy reconstruction involving an initial procedure to fit a tissue expander and then a second surgery to replace the tissue expander with a permanent breast implant. This study will compare this standard treatment option with the additional use of ADM (Strattice™) as surgical mesh reinforcement.

Strattice™ Tissue Matrix is a porcine dermis-derived biologic (pig skin) surgical mesh used in surgery to help support the lower outer part of the breast, providing a scaffold, or framework, which allows the body's own cells and blood vessels to grow into it. It gradually becomes part of the body as over time Strattice™ is replaced by the body's own tissue. Strattice™ Tissue Matrix itself contains no human cells. Strattice™ has been indicated for use in post-mastectomy breast reconstruction with implant since 2008 and carries a CE mark, which means it has been approved for use in the European Economic Area (EEA). It is not an experimental product. Strattice™ is marketed by LifeCell™ EMEA Ltd. who are providing the product free of charge for this study.

Strattice™ is routinely used in breast reconstruction in some European countries, including in the UK, but is not routinely available for patients undergoing treatment for breast cancer in Oxford University Hospitals (OUH) NHS Trust due to cost implications. The results of this study may support a case for the routine use of the product if the cost of the product is offset by the reduction in number of subsequent operations or reduced hospital visits. The study will evaluate the two treatment arms in terms of effectiveness, safety and efficacy endpoints as well as economic considerations.

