## 6.5 Schedule of Events

Eligible patients will be approached about the study and given a Patient Information Sheet to read and will be given opportunity to discuss the trial with the Clinician or Research Nurse. If the patient decides to participate they will be asked to sign an Informed Consent Form. It is at this point that the patient enters the study and is randomized. A letter will be sent to the patient's GP informing them of their participation in the study and treatment allocation.

Patients will attend a Baseline visit at enrollment where they will undergo clinical assessments and complete a Baseline CRF and Questionnaires. This can be at the same time as signing of the ICF or can be at a separate visit. After treatment allocation patients will be booked in for surgery as usual. All patients randomised to the standard treatment (non-Strattice™) will undergo a two stage post-mastectomy reconstruction using an expander prior to the implant being fitted. Patients randomised to the treatment arm using Acellular Dermal Matrix (with Strattice™) will either undergo the same two-stage reconstruction but with the addition of the Strattice™ mesh, or a single-stage post-mastectomy direct-to-implant reconstruction in which the Strattice™ is fitted in the same procedure as the implant. The type of procedure used will be dependent on clinical factors such as the size and shape of the breasts and the surgeon will make this decision on a case-by-case basis.

Therefore, patients receiving single stage direct-to-implant IBR will have a single surgical visit (Group B only) whilst those patients receiving two-stage IBR using an expander will have two surgical procedures in separate visits (all Group A patients and some Group B patients).

After surgery, patients in both groups will be discharged home with the drain in place (current standard of care) and the breast care nurses will remove the drain as per standard guidelines. The patients will be contacted by the research nurse after their discharge to assess whether they need to be brought back to hospital for an earlier review. Patients undergoing implant reconstruction with ADM are likely to have the drains left in situ for a longer duration to allow the ADM to adhere to the overlying skin

envelope and therefore ensure integration of the product. However, this should not lead to increased hospital stay and patients in both treatment arms will have the drained removed within 1-4 weeks

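### Section 6.4 contradicts itself, and section 6.5, on whether Group A patients may have single-stage reconstruction, so the protocol does not settle whether the trial compares ADM or an ADM strategy that includes staging

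*Protocol*

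**What the plan says.** Two consecutive paragraphs of Protocol section 6.4 (Study settings and procedures) describe how the arms are operated on.

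- **First rule.** "Patients randomized to Group A (non-Strattice™) will be reconstructed with expander or anatomical gel implants without ADM, using complete muscle coverage". Group B may likewise receive either device, with partial muscle coverage and ADM. Allocation concerns ADM only, "so both expander and direct-to-implant techniques will be utilized in both groups, depending on the quality of skin flaps at time of surgery".
- **Second rule.** "All patients randomised to Group A, the standard (non-Strattice™) treatment will undergo a two stage post-mastectomy reconstruction using an expander". Group B may be two-stage with ADM or single-stage. The basis for choosing also changes: "The type of procedure used will be dependent on clinical factors such as the size and shape of the breasts".

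Section 6.5 (Schedule of Events) repeats the second rule: "patients receiving single stage direct-to-implant IBR will have a single surgical visit (Group B only"), while those with an expander "will have two surgical procedures in separate visits (all Group A patients and some Group B patients").

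Three other places bear on the point:

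- Section 4 gives usual practice for one site only: "Currently in Oxford, most patients receiving Immediate Breast Reconstruction (IBR) using implants will undergo a two stage post-mastectomy reconstruction". Section 5.1 lists five sites, four of them in Sweden, and their usual practice is not described.
- The sample-size text in section 5.4 defines the arms by ADM and muscle coverage and does not mention staging.
- Section 6.2 lists total procedures, planned and unplanned together, and a 24-month cost comparison as secondary outcomes.

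**The concern.** Both rules cannot hold. Under the first, a Group A patient with good skin flaps may go straight to an implant; under the second, the same operation is a protocol deviation. A site can follow either paragraph and point to the text in support.

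The rules also lead to different conclusions. Under the first, the arms differ in ADM together with the muscle coverage that goes with it, and staging is open to both. Under the second, the arms differ in ADM plus permission to omit a stage, which only Group B has. Total procedures and 24-month cost then carry a difference fixed by the protocol. This matters because section 4 hopes to support routine use of the product if fewer later operations or visits offset its price.

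**Working it through.** **1. The plan's own figure.** The protocol states no figure for staging. Its only related number is the sample size, and that is not at issue. With 60% against 30%, two-sided 5% and 80% power, the normal approximation with pooled variance under the null gives 42 per arm. With the continuity correction it gives 49 per arm, or 2 × 49 = 98, the stated total.

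**2. The statements side by side.**

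| Place | Group A | Group B | Basis for choice |
|---|---|---|---|
| 6.4, first rule | expander or direct-to-implant | expander or direct-to-implant | skin flaps, at surgery |
| 6.4, second rule | two-stage for all | two-stage or single-stage | breast size and shape, among other clinical factors |
| 6.5 | two-stage for all | two-stage or single-stage | breast size and shape, among other clinical factors |

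The first row conflicts with the other two for Group A. No text gives one rule priority.

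**3. Planned procedures under the second rule.** Let s be the share of Group B that is two-stage.

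- Group A: 2 planned procedures per patient.
- Group B: 2s + 1(1 − s) = 1 + s.
- Built-in difference: 2 − (1 + s) = 1 − s.

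The protocol does not give s, so these values are assumptions:

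- s = 0.5: 1 − 0.5 = 0.5 procedures per patient.
- s = 0.3: 1 − 0.3 = 0.7 procedures per patient.
- Limits: 0 if all of Group B is staged, 1 if none is.

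With 120 recruited and equal arms (120 / 2 = 60 each), that is 60 × 0.5 = 30 or 60 × 0.7 = 42 extra planned operations in Group A, before any complication.

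**4. Planned procedures under the first rule.** With staged shares a in Group A and b in Group B, the difference is (1 + a) − (1 + b) = a − b. The surgeon knows the allocation, so a and b may still differ, but the protocol does not fix that difference.

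**5. A mixture of rules.** If a share w of patients is treated at sites using the second rule, the pooled difference is w(1 − s) + (1 − w)(a − b). It lies between the two answers and depends on which sites read which paragraph.

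**The case against.** The strongest reply is that the protocol leans towards the second rule and treats staging as part of what ADM offers. The all-two-stage text appears in 6.4, is spelled out again in 6.5, and fits the statement there that only the surgical visits differ between groups. The background presents more single-stage reconstruction and less need for expanders as purposes or reported benefits of ADM. Section 6.2 counts planned procedures deliberately. On that reading, 1 − s is part of the treatment effect and not a bias.

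Most of this stands. It makes the strategy reading plausible, but it does not remove the contrary paragraph, and neither the objective nor the sample-size text says that staging belongs to the comparison.

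A reader might infer more than the documents support:

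- *That the comparator is undefined.* Group A is consistently full muscle coverage without ADM. Only its staging is contradicted.
- *That ADM is confounded with staging.* Staging is chosen after allocation, so the comparison of the two packages remains randomised. Only attribution to ADM alone is lost, and by design only under the second rule.
- *That early quality of life and photographs are distorted.* No questionnaire is given at 3 months, and the protocol does not say when the second stage takes place.
- *That the primary endpoint is biased by a known amount.* Appendix 1 counts exchange from a permanent expander to a gel implant as unplanned, but the protocol does not say whether a planned second stage is scored that way or how often such exchanges occur. Any figure would rest on assumed shares.
- *That sites will in fact diverge.* The text permits it; nothing shows that it happens.

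**Conclusion.** The point holds as an internal contradiction: as written, the protocol cannot be followed consistently on how Group A is staged. Validity of the randomised comparison is not at risk; what is at risk is the meaning of the result. Under the second rule, the secondary outcomes of total procedures and 24-month cost describe ADM together with the option to omit a stage. The size is 1 − s planned procedures per patient, 0.5 to 0.7 for assumed staged shares of 0.5 to 0.3 in Group B. That range rests on s, which the documents do not give, and on all of Group A being two-stage. If sites apply different rules, the pooled estimate mixes two questions. The sample size is unaffected.

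**What to change.** 1. Reconcile the two paragraphs of section 6.4 with section 6.5 into one staging rule per arm that holds at all five sites, including the basis on which technique is chosen. This review does not say which rule is right.
2. State in the objective, and carry into the conclusion, whether the comparison is ADM itself (with its muscle coverage) or the ADM strategy including staging.

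The cost is protocol wording. If the strategy reading is kept, the claim about total procedures and cost is narrower than an effect of ADM.

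Optionally, the surgeon's intended staging could be recorded before randomisation, as one baseline CRF item. It would be of limited use: a decision based on skin flaps at surgery cannot be captured beforehand, and if all of Group A is staged the intention there is hypothetical. Actual staging must not enter the logistic regression in section 5.4 as an adjustment covariate. It arises after randomisation, and under the second rule Group A contains no single-stage patients.

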## 6.5 Schedule of Events

Eligible patients will be approached about the study and given a Patient Information Sheet to read and will be given opportunity to discuss the trial with the Clinician or Research Nurse. If the patient decides to participate they will be asked to sign an Informed Consent Form. It is at this point that the patient enters the study and is randomized. A letter will be sent to the patient's GP informing them of their participation in the study and treatment allocation.

Patients will attend a Baseline visit at enrollment where they will undergo clinical assessments and complete a Baseline CRF and Questionnaires. This can be at the same time as signing of the ICF or can be at a separate visit. After treatment allocation patients will be booked in for surgery as usual. All patients randomised to the standard treatment (non-Strattice™) will undergo a two stage post-mastectomy reconstruction using an expander prior to the implant being fitted. Patients randomised to the treatment arm using Acellular Dermal Matrix (with Strattice™) will either undergo the same two-stage reconstruction but with the addition of the Strattice™ mesh, or a single-stage post-mastectomy direct-to-implant reconstruction in which the Strattice™ is fitted in the same procedure as the implant. The type of procedure used will be dependent on clinical factors such as the size and shape of the breasts and the surgeon will make this decision on a case-by-case basis.

Therefore, patients receiving single stage direct-to-implant IBR will have a single surgical visit (Group B only) whilst those patients receiving two-stage IBR using an expander will have two surgical procedures in separate visits (all Group A patients and some Group B patients).

After surgery, patients in both groups will be discharged home with the drain in place (current standard of care) and the breast care nurses will remove the drain as per standard guidelines. The patients will be contacted by the research nurse after their discharge to assess whether they need to be brought back to hospital for an earlier review. Patients undergoing implant reconstruction with ADM are likely to have the drains left in situ for a longer duration to allow the ADM to adhere to the overlying skin

envelope and therefore ensure integration of the product. However, this should not lead to increased hospital stay and patients in both treatment arms will have the drained removed within 1-4 weeks

Patients will attend follow-up appointments at 1-4 weeks, and 3, 6, 12 and 24 months after their initial surgery (current standard care). During these visits the patient will undergo clinical assessments and will be asked to complete follow-up CRF's and questionnaires.

Where possible all study visits will coincide with routine clinical appointments. With the exception of the difference in surgical visits, all other trial visits and procedures are identical for both Group A and B.

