## SCHEDULE OF EVENTS

|                                        | Screening | Visit 0
Baseline | Surgery /
Post-op  | Visit 1
(1-4 weeks) | Visit 2
(3 months) | Visit 3
(6 months) | Visit 4
(12 months) | Visit 5
(24 months) |
|----------------------------------------|-----------|---------------------|-----------------------------------|------------------------|-----------------------|-----------------------|------------------------|------------------------|
| PIS provided                           | x         |                     |                                   |                        |                       |                       |                        |                        |
| ICF signed                             | x         |                     |                                   |                        |                       |                       |                        |                        |
| Patient randomised                     | x         |                     |                                   |                        |                       |                       |                        |                        |
| Eligibility checked                    | x         | x                   |                                   |                        |                       |                       |                        |                        |
| Medical history                        |           | x                   |                                   |                        |                       |                       |                        |                        |
| Clinical examination /
measurements |           | x                   | x                                 | x                      | x                     | x                     | x                      | x                      |
| Drain removed                          |           |                     |                                   | x                      |                       |                       |                        |                        |
| Photographs taken                      |           | x                   |                                   |                        | x                     | x                     | x                      | x                      |

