| Case Report Form (CRF)                 |           | x                   | x                                 | x                      | x                     | x                     | x                      | x                      |
| QoL Questionnaire -
EORTC QLQ-C30   |           | x       |                                   |                        |                       | x                     | x                      | x                      |
| QoL Questionnaire –
EORTC BR23      |           | x       |                                   |                        |                       | x                     | x                      | x                      |
| QoL questionnaire –
EORTC BRR26     |           |                     |                                   |                        |                       | x                     | x                      | X                      |
| Adverse Events                         |           |                     | x                                 | x                      | x                     | x                     | x                      | X                      |

 – Baseline QoL questionnaires should be completed before randomization

 – Patients undergoing single-Stage direct to implant IBR will have one surgical visit. Patients undergoing two-stage IBR with expander will attend two separate surgical visits.

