## **9 Study Data Collection**

### **9.1 Case Report Forms (CRF's)**

At each visit the investigator will obtain the required data to complete the Case Report Form (CRF). The CRF will record clinical and patient details such as medical history, demographics, breast measurements, and the presence of any pain or infection. There is a separate CRF for each visit, including at Baseline and all follow-up visits (1-4 weeks, 3, 6, 12 and 24 months). CRF's should be completed with the patient at their routine clinical appointment or by the clinical care team where appropriate. The baseline CRF should be completed prior to randomization.

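### Section 6.5 and the schedule randomise at consent and allow a separate, hence later, baseline visit, although 9.1, 9.2 and footnote 1 require baseline CRF and QoL before randomisation

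*Protocol*

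**What the plan says.** Several places fix the order of consent, baseline and randomisation.

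- Section 6.2: "Informed consent must be obtained before any study-related activities take place".
- Section 6.3: "After signing and dating the Informed Consent Form (ICF) the patient can be entered into the study and randomized". Completed baseline forms are not named as a condition. The same section adds: "Patients should be informed of their allocation promptly".
- Section 6.5, directly after describing signature of the consent form: "It is at this point that the patient enters the study and is randomized". Of the baseline visit, where the clinical assessments, baseline CRF and questionnaires are done, it says: "This can be at the same time as signing of the ICF or can be at a separate visit".
- Schedule of Events table: the row "Patient randomised" is ticked under Screening. Medical history, examination, photographs, CRF, QLQ-C30 and BR23 are first ticked in the next column, Visit 0 Baseline. Eligibility is ticked in both columns.
- Schedule footnote 1: "Baseline QoL questionnaires should be completed before randomization".
- Section 9.1: "The baseline CRF should be completed prior to randomization". Section 9.2 gives the same rule for the baseline questionnaire.

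**The concern.** A site that uses the separate baseline visit allowed by 6.5 cannot also obey 9.1, 9.2 and footnote 1.

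The allocation is disclosed to the patient, and QLQ-C30 and BR23 are self-reported. A patient who already knows whether she will receive the matrix may answer differently from one who does not, and the shift may differ between arms. The questionnaire then no longer serves as a pre-allocation baseline. Quality of life is a listed secondary outcome (section 6.2, Secondary outcome measures), and these two are its only instruments with a baseline value. No later analysis can recover an answer given before allocation if none was collected.

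**Working it through.** No arithmetic applies: the point depends on no rate, effect size or sample size, and the protocol gives no figure to reproduce. The check sets the two orders side by side.

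| Step | 6.3, 6.5 and schedule columns | 9.1, 9.2 and footnote 1 |
|---|---|---|
| 1 | Consent | Consent |
| 2 | Randomisation | Baseline CRF, QLQ-C30, BR23 |
| 3 | Prompt disclosure of allocation | Randomisation |
| 4 | Baseline CRF, QLQ-C30, BR23, if Visit 0 is separate | Disclosure |

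**Separate baseline visit.** Section 6.5 calls the visit separate and does not say whether it is earlier or later. Section 6.2 (Informed consent) settles this: baseline forms are study activities and cannot precede consent. Since 6.5 ties randomisation to consent, a separate visit must come after both. The column order of the schedule agrees. The two orders therefore cannot both hold.

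**Same-day baseline visit.** The orders are compatible only if the forms are completed between signature and randomisation. Section 6.5 does not say so.

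**Text that could settle the conflict.** Section 6.3 permits randomisation after consent without requiring it at once, so a site may wait, but nothing there tells it to. Footnote 1 states the intended rule, but only for the questionnaires, and it sits under a table whose columns run the other way. The outline of randomisation steps in Appendix 2 does not mention baseline completion.

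**Study ID.** Sections 6.3 and 10.1 issue the ID on randomisation, and 6.3 wants it on all CRFs and questionnaires. Taken literally, this also favours randomising first. It is not decisive: the consent form must carry the ID too and is signed before the ID exists, so the number can be added afterwards.

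**Which data are exposed.** QLQ-C30 and BR23 have a baseline and follow-up at 6, 12 and 24 months, so any comparison at those times that uses baseline is open to the problem. BRR26 is first given at 6 months and has no baseline. Unplanned reoperations, the primary endpoint, are counted after surgery, and the sample size rests on assumed reoperation rates of 60% and 30%. None of these uses the baseline questionnaires.

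**The case against.** The best defence is that the baseline-first rule is stated three times, once as a footnote on the very cells of the schedule that matter. Section 6.3 is only permissive, and 6.5 places the baseline visit at enrolment and mentions booking of surgery after allocation only once the baseline visit has been described. On this view the intended order is clear, and the fault is loose narrative and one misplaced tick. Much of this stands: the authors evidently wanted baseline data first, so this is an inconsistency in the text and not a deliberate choice of post-allocation baseline. But 6.5 and the schedule are what site staff work from, and both put randomisation first.

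Three stronger readings are tempting and are not supported.

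- *Patients found ineligible at Visit 0 become exclusions after randomisation.* Eligibility is also ticked at Screening, section 6.3 has the system verify the criteria before it allocates, and no passage removes patients found ineligible at Visit 0. Ineligibility is not among the listed grounds for withdrawal in section 6.7.
- *Every quality-of-life comparison is biased.* The protocol specifies no baseline-adjusted or change-from-baseline analysis. A comparison of post-operative scores alone does not use baseline, and bias also requires a separate Visit 0 and answers that shift with knowledge of the arm.
- *The bias can be put at some number of points.* The protocol gives no basis for one.

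**Conclusion.** The contradiction is in the text and should be corrected. Where Visit 0 is a separate visit, a site following 6.5 and the schedule would collect baseline QLQ-C30 and BR23 from patients who know their allocation. That can bias any quality-of-life comparison that uses baseline.

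The size is unknown. It depends on how many patients have a separate Visit 0, on whether sites follow 6.5 or 9.1 and 9.2, and on how far knowledge of the arm moves the answers; the protocol informs none of these. The consequence is confined to secondary baseline data. The correction is worth making because the loss cannot be repaired afterwards and costs very little to prevent.

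**What to change.** State one order in 6.3, 6.5 and the schedule: consent, eligibility check, baseline CRF and questionnaires, randomisation, disclosure to the patient. In detail:

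- Section 6.5: replace the sentence that ties randomisation to signature with one that places it after the baseline forms are complete, whether Visit 0 is on the same day or separate.
- Section 6.3: name completed baseline CRF and questionnaires as a condition for randomising.
- Schedule: move the randomisation tick to the end of Visit 0. Keep the Visit 0 eligibility check, which then falls before allocation.
- Sections 6.3 and 10.1: align the Study ID sentence so that baseline forms can be completed before the ID is issued and labelled afterwards.
- Optional: a field in the randomisation form confirming that the baseline forms are complete.

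The cost is a wording and table change. Allocation may come a few days later for patients whose baseline visit is separate.
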